# Stem cell therapy for idiopathic pulmonary fibrosis: a protocol proposal

**DOI:** 10.1186/1479-5876-9-182

**Published:** 2011-10-21

**Keywords:** stem cells, adipose tissue, stromal vascular fraction, idiopathic pulmonary fibrosis, therapy, endobronchial infusion, prospective, nonrandomized phase Ib clinical trial

## Abstract

**Background:**

Idiopathic pulmonary fibrosis represents a lethal form of progressive fibrotic lung disorder with gradually increasing incidence worldwide. Despite intense research efforts its pathogenesis is still elusive and controversial reflecting in the current disappointing status regarding its treatment. Patients and Methods: We report the first protocol proposal of a prospective, unicentric, non-randomized, phase Ib clinical trial to study the safety and tolerability of the adipose-derived stem cells (ADSCs) stromal vascular fraction (SVF) as a therapeutic agent in IPF. After careful patient selection based on functional criteria (forced vital capacity-FVC > 50%, diffuse lung capacity for carbon monoxide-DL_CO _> 35% of the predicted values) all eligible subjects will be subjected to lipoaspiration resulting in the isolation of approximately 100- 500 gr of adipose tissue. After preparation, isolation and labelling ADSCs-SVF will be endobronchially infused to both lower lobes of the fibrotic lungs. Procedure will be repeated thrice at monthly intervals. Primary end-point represent safety and tolerability data, while exploratory secondary end-points include assessment of clinical functional and radiological status. Results: Preliminary results recently presented in the form of an abstract seem promising and tantalizing since there were no cases of clinically significant allergic reactions, infections, disease acute exacerbations or ectopic tissue formation. In addition 6 months follow-up data revealed a marginal improvement at 6-minute walking distance and forced vital capacity.

**Conclusions:**

Adipose tissue represents an abundant, safe, ethically uncontested and potentially beneficial source of stem cells for patients with IPF. Larger multicenter phase II and III placebo-controlled clinical trials are sorely needed in order to prove efficacy. However, pilot safety studies are of major importance and represent the first hamper that should be overcome to establish a rigid basis for larger clinical trials.

## Background

IPF is a refractory and lethal form of pulmonary fibrosis characterized by fibroblast proliferation, extracellular matrix deposition, and progressive lung scarring, and comprises the histopathologic pattern of usual interstitial pneumonia (UIP). The incidence of IPF is estimated at 6.8 to 16.3 cases per 100, 000 per year in the United States, and the mean survival from the time of diagnosis is 3 to 5 years regardless of treatment, showing a prognosis worst that than seen in patients lung cancer [1-3].

Although the etiology and pathogenesis of IPF remain poorly understood, current research suggests that the mechanisms driving IPF reflect abnormal, deregulated wound healing in response to multiple sites of ongoing alveolar epithelial injury, involving increased activity and possibly exaggerated responses by a spectrum of proinflammatory and profibrogenic factors [4-10]. So far, despite intense research efforts and clinical trials, there is still no effective treatment that can prolong the survival of patients with IPF [11-14]. Conventional therapeutic approach includes combination of corticosteroids, anti-oxidants, immunosuppressants and immunomodulatory anti-fibrotic agents [11-16]. However, the only, so far, therapeutic approach that has been proven effective in terms of prolonging patient's survival is lung transplantation. Nonetheless, not all the patients with IPF are eligible for lung transplantation whereas there is a significant proportion of these patients that finally succumb while waiting in a lung transplantation list. Therefore, there is critical need for more effective and reliable therapeutic modalities.

Mesenchymal stem cells (MSCs), of different cellular origins (umbilical cord, bone marrow, adipose tissue), represent one of the most challenging and promising areas of novel therapeutic strategies that have been recently applied apart from cosmetic reasons, in several chronic, incurable, fatal diseases such as diabetes mellitus type II, Parkinson's disease, congestive heart failure, renal failure, osteoarthritis and myocardial infarction [17-23].

Of special interest are adipose-derived stem cells (ADSCs)- stromal vascular fraction (SVF), as they present with fruitful therapeutic advantages against bone marrow stem cells including ease of extraction, higher content of MSCs and ex-vivo expandability [21,22]. Currently we have witnessed an explosion of experimental data supporting the migratory, differentiative and reparative capacity of MSCs in animal models of lung inflammation and fibrosis [21,22]. In particular, a number of studies have investigated the role of umbilical cord MSCs as a treatment option in the experimental model of pulmonary fibrosis and showed their potency to be differentiated under a specific micro-environment, into alveolar type II epithelial cells [24] whereas mice adult-stem cells can attenuate lung fibrosis in the bleomycin-model of pulmonary fibrosis [25,26]. Furthermore, repeated intravenous administrations of human and mouse ADSCs resulted in substantial beneficial effects in a model of inflammation and injury induced by cigarette-smoke exposure [27]. More intriguingly a recent report demonstrated for the first time rigid evidence supporting the presence of resident stem cells within human lungs that exert beneficial role in tissue homeostasis and regeneration in animal models [28].

Despite promising therapeutic results arising from experimental studies safety issues and concerns coupled with major controversies regarding IPF pathogenesis, have severely hampered chest physicians' efforts to apply cell-based therapies for the treatment of this dismal disease. To address the above concerns and to establish a rigid basis for future efficacy trials, we are reporting the first protocol proposal of a nonrandomized, unicentric, dose-ranging phase Ib safety study of endobronchial infusion of autologous ADSCs-SVF in IPF patients with moderate disease severity.

### Aim and hypothesis

The aim of the study is to investigate the hypothesis that endobronchial autologous infusion of ADSCs-SVF cells is safe, feasible and well tolerated as a therapeutic modality in IPF patients. Our main hypothesis is that the above procedure can provide to the targeted areas of epithelial injury and excessive fibrotic tissue with adequate number of minimally manipulated multi-potent SVF cells with increased anti-inflammatory paracrine activity as well as regenerative capacity overcoming the fear and concern of undesirable alterations of MSCs during ex-vivo cellular expansion, including contaminations, tumor, ectopic tissue formation and lung toxicity resulting from undesirable engraftment in the microvasculature.

### Patients and methods

In our phase Ib dose escalating study will participate 12 with IPF, respectively, based on the recently published diagnostic criteria of ATS/ERS (2011), of mild to moderate disease severity as estimated functional parameters including forced vital capacity (FVC) > 50% and diffusing lung capacity for carbon monoxide (DL_CO_) > 35% of the predicted normal values. All patients will sign an informed consent form where they will agree to their participation in the study and the anonymous usage of their biological fluids for research purposes (see inclusion criteria below).

### Inclusion criteria

Patients with a histologic or radiologic pattern typical of usual interstitial pneumonia will be included after other causes of fibrosis are ruled out.

The inclusion criteria are:

1. Age 18 to 75 years (both inclusive),

2. A high-resolution computed tomography (HRCT) scan that is very suggestive or consistent with a probable diagnosis of usual interstitial pneumonia.

3. Bronchoalveolar lavage must be performed at any time before inclusion and must have failed to show features supporting alternative diagnoses.

4. The duration of the disease should be more than three months, and bibasilar inspiratory crackles should be present. In addition, the following functional abnormalities have to be present: a dyspnea score of at least 2 on a scale of 0 (minimum) to 10 (maximum), FVC > 50% of the predicted normal value and DLco > 35% of the predicted value.

5. Patients willing to sign an informed consent form where they will agree to their participation in the study and the anonymous usage of their biological fluids for research purposes according to the Declaration of Helsinki.

6. Patients under treatment with n-acetylcysteine or pirfenidone should discontinue drug and enter a wash-out period for at least 6 weeks prior study enrolment.

### Exclusion criteria

1. IPF patients of severe disease based on the baseline functional data, meaning those with FVC < 50% predicted normal value and DLCO < 35%predicted normal value.

2. Patients diagnosed with lung cancer or with an evidence of active malignancy, or prior history of active malignancy that has not been in remission for at least 5 years

3. Patients with documented history of uncontrolled heart, renal or hepatic failure,

4. Patients with serious neurological abnormalities including stroke and myasthenia Gravis

5. Patients under anti-coagulants or in serious emaciation.

6. Patients with active infections.

7. Patients unable to be regularly followed up including those with serious psychiatric disorders.

8. Patients unwilling to sign informed consent form

### Study Methodology

**1) Approval by Local Ethics and Scientific Committee: **Original protocol has already been approved by the Local Ethics and Scientific Committee of the University Hospital of Alexandroupolis, Democritus University of Thrace, Greece (reference number EHD33/1SC/16-02-2010)

**2) Inform consent**: Patients willing to sign an informed consent form where they will agree to their participation in the study and the anonymous usage of their biological fluids for research purposes according to the Declaration of Helsinki.

**3) Physical and laboratory examination: **All patients will undergo a detailed physical and laboratory examination including: arterial blood gases, electrocardiogram (ECG), estimation of vital signs (blood pressure, temperature, breaths and beats per minute) as well as routine laboratory tests, including white blood cell count and differential count, red blood cell count, liver and renal function, serum C-reactive protein. Patients will undergo spirometry and chest HRCT, at screening to evaluate the functional and radiological severity of the disease and to localize the areas of the lungs where the infusion of SVF cells will be targeted to (Figure 1).

**Figure 1 F1:**
[figure not shown]
**Step-up procedure of protocol proposal of the endobronchial infusion of ADSCs in patients with IPF starting with patients' screening and enrolment and ending with follow-up period**. Abbreviations: 6MWT: 6-minute walking test, ABGs: Arterial blood gases, ADSCs: Adipose-derived stem cells, CAT: Cough Assessment Test, DL_CO_: Diffuse Lung Capacity for carbon monoxide FVC: Forced Vital Capacity, HRCT: High Resolution Computed Tomography, MRC: Medical Research Council- SGRQ: Saint George's Research Questionnaire, UIP: Usual Interstitial Pneumonia (histologic or radiologic)

**4) Lipoaspiration and isolation of ADSCs-SVF: **All eligible patients will undergo lipoaspiration under general anesthesia in a sterile surgical operating room setting. 50 mL of blood in EDTA will be taken to prepare platelet rich plasma (PRP). Approximately 100 - 500 gr of adipose tissue will be isolated from the above procedure performed by a plastic surgeon. Enzyme dissolution procedure of the adipose tissue, using collagenase type I solution under agitation for 2 hours plus 10 cc of lecithine followed by two centrifugations at 100 g for 10 minutes the first and at 1800 g for 10 minutes the second, will be performed to separate the stromal cell fraction (pellet) from adipocytes. The pellets will be treated with red lysis buffer. The final pellet will be re-suspended and a small volume of suspension will be used for flow cytometry analysis, counting CD29, CD73, CD90, CD34, CD105, positive cells and CD14, CD31 and CD45 negative cells in Coulter Epics XL/MCL. 10 mL of the suspension will be used for bacterial check with the BacT/Alert system (with colorimetric carbon dioxide detector). In the case of an infected sample the microorganism will be identified with VITEK 2 Compact 15 and will be excluded. A volume of DMSO solution will be added in the remaining suspension so that the final volume contains 10% DMSO and 2% Haes-steril 200. The cells will be cryo-preserved gradually and stored in cryovials, air-tightly sealed with cryoflex membrane. The vials will be placed in constant temperature in liquid nitrogen and will be stored there. Viability of the cells will be estimated by tryphan blue. A total of 3-5 × 10^6 ^cells per gram of adipose tissue is expected to be isolated. Based on the current literature [29], since SVF represents an heterogeneous cell population it is anticipated that approximately 50-70% of the total number of isolated cells to be of mesenchymal origin meaning CD29, CD105, CD90, CD73 positive and CD34, CD45 negative cells and 20-30% mature endothelial (CD31 and positive) and hematopoetic (CD34 positive) cells.

**5) Activation of ADSCs- SVF: **ADSCs- SVF though large in number lie dormant within the adipose tissue and therefore they require activation to come into full functionality for more successful implantation into the host tissue and to begin self-renewal by cell division and formation of other cell types by differentiation and transdifferentiation. In order to increase the anti-inflammatory, angiogenic, anti-apoptotic and perhaps regenerative potential of ADSCs we will apply a two-step activation procedure: a) Activation through autologous PRP. Isolated SVF cells will be subjected to full activation using autologous PRP derived from 50 ml of peripheral blood drawn from each patient. PRP as a storage vehicle of growth factors, is a new application of tissue engineering which was considered for the application of growth factors. PRP is a concentration of platelets in plasma developed by gradient density centrifugation. It contains many growth factors, such as vascular endothelial growth factor (VEGF), epidermal growth factor (EGF), insulin-like growth factor (IGF), Keratinocyte growth factor (KGF), hepatocyte growth factor (HGF) and stromal derived factor (SDF), that may potentially accelerate proliferation of stem cells, improve their chemotactic activity and facilitate their engraftment to the multilayer vessels in order to exert their beneficial properties. b) Activation using low level laser irradiation (5 J/cm^2^). The syringe containing isolated SVF cells enriched with PRP solution will be placed a laser device specifically manufactured for the purposes of this study by Adistem Ltd. Photobiostimulation has been proposed to exert several biological actions including upregulation of angiogenic (VEGF) and anti-inflammatory (IL-1 receptor antagonists, SDF) mediators as well as down-regulation of inflammatory cytokines including tumor necrosis factor(TNF)- alpha, IL-1, 6 and 8 and reactive oxygen species [30] (Figure 1).

**6) Randomization of patients depending on the level of treatment: **To define and standardize the optimal dose regimen that will be both safe and effective we will randomize our 12 patients in the phase I trial into two categories depending on the level of treatment, meaning the number of SVF cells infused per bronchoscopy. In particular we will define as low treatment level the infusion of 0.5 × 10^6 ^SVF cells per kgr of body weight per infusion meaning a total of 1.5 × 10^6 ^SVF cells per kgr of body weight (approximately 120 × 10^6 ^cells in total) and as high treatment level the infusion of 1 × 10^6 ^of SVF cells per kgr of body weight per infusion meaning a total of 3 × 10^6 ^SVF cells per kgr of body weight (approximately 240 × 10^6 ^cells in total). The dose regimen will be based on data arising from previous published studies in patients suffering from myocardial infarction where a dose escalation procedure was applied using a single infusion of 0.5, 1.6 and 5 millions bone marrow mesenchymal stem cells (BM-MSCs) per body weight. Results from the former study demonstrated the absence of a dose-dependent effect while no differences in side-effects between the three studied groups were observed [20]. Moreover, an ongoing clinical trial (the TIME study), with a registration number of NCT00684021, is studying the safety and efficacy of one single dose of intravenously infused 150 million cells in total (meaning 0.5 million cells per kgr of body weight) in patients who had experienced a heart attack. Finally, a recent ongoing clinical trial by Matthay et al [31]. is estimating the safety of two single dose regimens of 5 and 10 million BM -MSCs per kgr of body weight in patients with acute lung injury. Patients in the two randomization groups will be age, sex and disease severity (based on spirometry and HRCT criteria) matched. Our study dose-escalating regimen is in accordance with the existing safety data arising from both published and currently ongoing clinical trials (Figure 1).

**7) Labeling of ADSCs with ^99 m^Tc-HMPAO (^99 m^Tc-ceretec)**: To visualize ADSCs within the lung, in a representative number of patients (n = 4), we will label them with ^99 m^Tc-HMPAO (^99 m^Tc-ceretec) according to a modified protocol [32]. A fraction of isolated ADSCs will be diluted into a 5 cc syringe with sodium chloride 0.9% and incubated with a vial containing 0.5 mg of ceretec reconstituted with approximately 2.0 mCi of free technetium (^99 m^TcO_4_^-^) and prepared to be infused within the right lung. A second syringe containing unlabeled ADSCs and 5 mL sodium chloride 0.9% reconstituted with approximately 2.0mCi ^99 m^TcO_4_^- ^and prepared to be administered into the left lung serving as control sample. As depicted in Figure 2 and as was expected, signal intensity was much stronger in the right lung and this effect remained even 24 hours after the infusion, indicating the presence of ADSCs (Figure 1).

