### Primary end-points (Safety and Toxicity levels)

The procedure is safe and well tolerated by the patients, as reflected by the absence of signs compatible with infection, allergic reaction, disease acute exacerbation, and ectopic tissue formation, at 12 months after the first post-endobronchial infusion of SVF cells (total follow-up duration for each patients = 12 months).

In particular, patients will be subdivided into three categories depending on the level of toxicity, defined as:

**1) Low level**, including minor side effects such as increased cough, low fever (less than 37.5°C, skin allergic reactions)

**2) Medium level**, including non-life threatening allergic reactions, infections that do not require hospitalization, elevation of liver enzymes or creatinine serum levels.

**3) High level**, including death and/or life threatening major adverse events such as disease acute exacerbations defined as follows:

*a) *If the patient experiences a significant worsening of dyspnea and a decline in exercise tolerance associated with a 10% decrement of their FVC, a 10 mmHg change in PaO_2 _or 50% increase in their oxygen requirement, and a significant progression in their radiographic score between the three month clinic visits;

*b) *If the patient needs to be admitted to the hospital because of worsening respiratory failure requiring mechanical ventilation, worsening gas exchange, or presumed pulmonary infection.

*c) *If the patient develops ectopic tissue formation compatible with carcinogenesis as assessed by whole body computed tomography at 12 months after the first post-endobronchial infusion of SVF cells

Exploratory secondary end-points:

1) Assessment of Forced Vital Capacity (FVC%) predicted.

2) Assessment of Diffuse Lung Capacity for carbon monoxide (DL_CO_%) predicted.

3) Assessment of 6MWT.

4) Assessment of dyspnea scales (Borg, MRC) as well as health-related quality of life questionnaires (SGRQ)

5) Assessment of the disease extent and severity as reflected by chest high resolution computed tomography (HRCT) at 6 and 12 months post-bronchoscopy.

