### Statistical analysis

Statistical analysis will be performed using the SPSS 16.0 software. Safety and exploratory efficacy secondary end-points will be observed for each patient against the baseline values. A p value < 0.05 will be considered as statistically significant.

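### Two dose levels in 12 uncontrolled patients cannot define an optimal dose that is both safe and effective, and a general p<0.05 rule is uninformative for the incident safety events

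*Protocol article*

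**What the plan says.** Patients and methods fixes the size: "In our phase Ib dose escalating study will participate 12 with IPF". Study Methodology, item 6, says "we will randomize our 12 patients in the phase I trial into two categories depending on the level of treatment" and gives the purpose as "To define and standardize the optimal dose regimen that will be both safe and effective". The allocation ratio is not stated. Both levels are active and there is no untreated group.

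The Statistical analysis section is three sentences long. After naming the software, it says "Safety and exploratory efficacy secondary end-points will be observed for each patient against the baseline values" and then "A p value < 0.05 will be considered as statistically significant". It mentions no comparison between the two levels, and it does not exempt safety from the threshold.

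The primary end-point section treats safety differently. The procedure counts as safe and tolerated "as reflected by the absence of signs compatible with infection, allergic reaction, disease acute exacerbation, and ectopic tissue formation" at 12 months, and "patients will be subdivided into three categories depending on the level of toxicity". Efficacy measures are listed there as exploratory secondary end-points. Aim and hypothesis confines the aim to safety, feasibility and tolerability, and the abstract's conclusions leave proof of efficacy to later placebo-controlled trials.

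**The concern.** The dose purpose is a positive claim about what the trial will deliver, and it is larger than the rest of the document allows. To call a regimen effective, one needs a reference against which effect is measured. To call one of two regimens optimal, one needs to compare them and have a rule for choosing. The article supplies none of these, and 12 patients could not support them if it did.

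The second part concerns the analysis text. Infection, allergic reaction, acute exacerbation and ectopic tissue are events that arise after infusion. Comparing them with a baseline at which they are absent, at p<0.05, gives a test that would rarely flag harm, and its non-significance would say nothing about safety.

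At stake is what the trial may conclude. The Discussion presents the study as a source of pivotal safety data to speed larger trials. A reader could take from it an established dose, or a demonstrated absence of risk, that the data cannot provide.

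**Working it through.** **Inputs from the protocol article.** N = 12 and two dose levels (Patients and methods; Study Methodology item 6). Threshold 0.05 (Statistical analysis). Follow-up: "total follow-up duration for each patients = 12 months".

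**Assumptions, because the article does not give them.** 6 patients per level; two-sided tests; illustrative event risks. The sample size comes with no design inputs, so there is no planned power to reproduce.

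**1. Separating two levels on an event, 6 v 6.** Two-sided Fisher p-values:
- 0/6 v 4/6: 2 × C(6,4)/C(12,4) = 2 × 15/495 = 0.061
- 0/6 v 5/6: 2 × C(6,5)/C(12,5) = 2 × 6/792 = 0.015
- 1/6 v 5/6: 0.080
- 1/6 v 6/6: 2 × 6/792 = 0.015

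Significance therefore needs 0 v 5, 0 v 6 or 1 v 6 (or the mirror image).

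Power for true risks of 10% v 40%:
- Lower-risk level: P(0) = 0.9^6 = 0.5314; P(1) = 6 × 0.1 × 0.9^5 = 0.3543
- Higher-risk level: P(5) = 6 × 0.4^5 × 0.6 = 0.0369; P(6) = 0.4^6 = 0.0041
- Power = 0.5314 × (0.0369 + 0.0041) + 0.3543 × 0.0041 = 0.0218 + 0.0015 = 0.023 (the mirror outcomes add a negligible amount)

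For 10% v 70%: P(5) = 0.3025 and P(6) = 0.1176, so power = 0.5314 × 0.4202 + 0.3543 × 0.1176 = 0.265.

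**2. Separating two levels on a continuous outcome, 6 v 6.** Two-sample t-test with 10 degrees of freedom and noncentrality d × √(6×6/12) = 1.732d. Power reaches 80% at d = 1.80 SD. It is 24% at 0.8 SD and 12% at 0.5 SD.

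**3. Safety events against baseline at p<0.05.** If every patient is event-free at baseline and r are later affected, the exact sign (McNemar) test gives p = 2 × 0.5^r:
- r = 5: 0.0625
- r = 6: 0.031

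At least 6 of 12 patients must be affected before p<0.05. The chance of 6 or more is 1.9% at a true risk of 20% and 11.8% at 30%.

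**4. What the event counts can say.** The exact (Clopper-Pearson) 95% upper limit after zero events is 1 − 0.025^(1/n):
- n = 12: 26.5%
- n = 6: 45.9%
- if the split is unequal, n = 4: 60.2%; n = 8: 36.9%

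Conversely, with a true risk of 10% the chance of seeing 0/12 is 0.9^12 = 28%.

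**5. Consistency within the article.** The dose purpose names effectiveness. The aim names only safety, feasibility and tolerability; the end-point list calls efficacy exploratory; the abstract defers proof of efficacy. These do not agree. Item 6 also reports that a cited cell-therapy study in myocardial infarction found no dose-dependent effect and no difference in side effects over 0.5 to 5 million cells, a tenfold range. The two levels here differ twofold.

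**The case against.** The strongest reply is that this is a phase Ib study. A small sample without a power calculation is normal there, no between-dose test is named, and a full protocol or analysis plan may hold the missing detail. The power figures above therefore do not show that a stated analysis is wrong. That is right, and small size alone is not the criticism. But the article does state the dose objective, and no detail in an unseen plan changes two levels, 12 patients and no control. The figures show the distance between that objective and the design.

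Three stronger readings are tempting and are not supported.

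- A reader might infer that the plan judges safety by p<0.05. It does not say so. The primary end-point section sets absence of listed events and three toxicity levels as the criterion, and the termination rule refers to high toxicity, not to a p-value. The fault is that the Statistical analysis section groups safety with efficacy under one comparison and then gives an unrestricted threshold.
- A reader might infer that no safety item has a baseline. Liver enzymes and creatinine appear in the medium toxicity level, and changes in FVC and PaO2 in the exacerbation definition; Table 1 schedules laboratory tests, lung function and blood gases at day 0. Comparison with baseline is usable for these.
- A reader might infer that every measure is tested at every visit, so that a false positive is nearly certain. The article does not say this. One test for each of the five listed end-points would give 1 − 0.95^5 = 23% if independent. A larger grid is a construction, and its tests would be correlated because changes in one measure share the same baseline.

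It is also fair that the article already labels efficacy exploratory and that a descriptive first safety estimate is feasible with 12 patients. Both stand, and both favour aligning the two sentences at issue with the rest of the text.

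**Conclusion.** The point holds for the dose objective and, in a limited form, for safety. The trial cannot define an optimal, safe and effective dose: with 6 per level, power is 2.3% for 10% v 40% and only 26.5% for 10% v 70%, and 80% power for a continuous outcome needs 1.8 SD. Nor is there a control group against which to call either level effective. These figures rest on the assumed equal split, two-sided testing and illustrative risks. The mismatch with the article's own aim rests on no assumption.

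For safety, the criterion in the primary end-point section is sound as a description. What needs correcting is that the general p<0.05 sentence can be read as covering incident events, for which it carries almost no information. Counts with exact intervals are informative but imprecise. This matters now because the Discussion already reports no clinically significant events among 12 enrolled patients as promising. Withdrawn patients are not replaced, so any loss would widen the limits further.

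**What to change.** In Study Methodology, item 6, replace the stated purpose with one the design can meet: to describe tolerability at the two levels, with no dose selected on efficacy.

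In Statistical analysis, separate safety from the exploratory end-points:
- Report safety events as counts by toxicity level and dose level, and overall, with exact 95% confidence intervals and no p-value criterion. State that 0/12 is compatible with a risk up to 26.5%, and 0/6 up to 45.9%.
- State that p<0.05 applies only to exploratory end-points, that such p-values are nominal, and that no efficacy claim will rest on them.

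Comparison with baseline can stay for laboratory and functional measures that have a day 0 value. The change costs wording only: no patients, visits or data are added. The downside is that the trial's claims become more modest.
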